##### Fourth Visit (End of the 12th Week)

3.7.5.4

On this visit, all measurements taken at the third visit will be measured, and the 3‐day food record sheet provided on the third visit will be collected.

##### Parameters Monitored Daily Throughout the Intervention

3.7.5.5

###### Overall Liking of Meals (Breakfast, Lunch, Dinner, and Snacks)

3.7.5.5.1

Perceived changes in the overall liking of meals associated with tablet intake will be assessed daily throughout the 12‐week intervention period. For each meal consumed with the tablet, participants will indicate whether they experienced a perceived change in overall liking (yes/no) and will rate their liking using the LAMS. Data will be collected via a Griffith University‐approved Qualtrics link. Participants will also record the date and time of tablet intake, the meal type (breakfast, lunch, dinner, or snack), the main constituents of the meal, and photographs of both served and leftover portions. Recording meal constituents will enable exploration of whether the effect of MB on overall liking varies across meal occasions and specific foods. Pre‐ and post‐meal photographs will provide qualitative information to support estimation of changes in food intake. Participants who prefer not to use the Qualtrics link will be provided with a hard copy version of the questionnaire containing identical items. The principal investigator will monitor submitted responses via Qualtrics daily.

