The taste modification property of MB has generated considerable interest due to its potential to influence overall liking of hypo‐palatable fruits and vegetables, hyper‐palatable SSBs, and mixed meals. By reducing the aversive qualities of sour and bitter tastes, MB may increase the preference for such fruits and vegetables. Indeed, evidence indicates that MB enhances the overall liking of individual sour‐tasting foods (Choi and Garza 2021; Choi and Park 2023); however, its effect on the preference and intake of other hypo‐palatable foods with a bitter taste profile is yet to be investigated. Beyond sour and bitter foods, MB has been shown to enhance the sweetness of already sweetened binary and trinary mixtures (Capitanio et al. 2011), which may result in a sensation of oversweetness. Consumer research suggests that when sweetness surpasses optimal levels and reaches the rejection threshold, preference and intake decline, potentially contributing to lower sugar consumption (Peng et al. 2023). Despite this, no study has examined the role of MB on changes to the overall liking of hyperpalatable SSBs. Furthermore, since most foods are consumed as mixed meals, it is notable that only one randomized cross‐over trial has investigated the effect of MB on the overall liking of mixed meals (Choi and Park 2023). In this study, a 400 mg dose of MB was selected based on its previously demonstrated effectiveness in individual sour‐tasting foods (Choi and Garza 2020, 2021). The same dose significantly increased liking for breakfast and dinner meals, which were specific to Korean‐American cultural diets, but showed no significant effect for lunch. The authors suggested that the effective dose of MB for modifying taste perception and overall liking may vary depending on the type of food. To the best of our knowledge, no dose‐comparison study has been conducted on taste perception, overall liking and intake for mixed meals.

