Phase 4	Change in the food preferences in a natural environment (i.e., at home)		Food‐liking questionnaire (FLQ)	FLQ is validated for the Australian population and contains 73 food items. It measured liking using a nine‐point hedonic scale, in which ‘like extremely’ was coded as ‘9’ and ‘dislike extremely’ was coded as ‘1’. If participants have never eaten a particular food or never experienced one of the listed items, they will be instructed to rate the item as “neither like nor dislike”. At baseline, sixth‐ and 12th‐week participants will score their liking of all listed food items in the FLQ. In the FLQ foods, items are grouped into 10 main categories based on the Australian Guide to Healthy Eating: grains, vegetables, fruits, dairy, animal‐based protein, plant‐based protein, fat and oil, sweet food, salty food, and alcohol. The mean in food‐liking scores for each food category will be generated (Wanich et al. 2020). Finally, the change in mean liking score for each food group, and the total change in food liking score, will be analyzed across measurement sessions	Wanich et al. (2018)
	Change in the overall liking of the specific or mixed food as a meal (breakfast, lunch, dinner, snack) in a natural environment (i.e., at home)		Any perceived change will be recorded using a yes/no response, and its magnitude will be quantified using Labeled Affective Magnitude Scale (LAMS)	Participants will record whether there is a perceived change in overall liking of meals due to the tables (yes/no). Then using LAMS, in which 0 represents the greatest imaginable dislike, and + 100 represents the greatest imaginable like, they will rate their liking of that specific meal. The scale will include options to select the meal type (breakfast, lunch, dinner, snack), a space to note down the major meal constituents, a space to attach photos of the meal (photo of a meal before and after eating, and the date and the time the meal was consumed)	Schutz and Cardello (2001)
	Perceived change in appetite		Perceived change in appetite (yes, no), and the direction of change (increase appetite or decreased appetite)	Along with the change in overall liking of meals, participants will note the effect of the tablet on their appetite (whether it helps them eat less, causes no change, or makes them eat more)	

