###### Appetite

3.7.5.5.2

Perceived changes in appetite associated with tablet intake will be assessed concurrently with overall liking for the same meals consumed with the MB or placebo tablet throughout the 12‐week intervention period. For each recorded meal, participants will indicate whether they experienced a perceived change in appetite (yes/no) and will specify the direction of change, indicating whether the tablet was perceived to increase or reduce food intake. Appetite responses will be collected using the same Qualtrics link (or hard copy form) and at the same meal occasion as the overall liking assessment. Detailed daily data collection procedures for the follow‐up period (Phase 4) are presented in Table S4.

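### Phase 4: the daily yes/no item on change in meal liking has no direction, so its analysed proportion cannot by itself show benefit, and the accompanying LAMS rates level rather than change

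*Protocol article*

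**What the plan says.** Two liking items are completed for every tablet meal. Section 3.7.5.5.1 states that "participants will indicate whether they experienced a perceived change in overall liking (yes/no) and will rate their liking using the LAMS". Table 3 (section 3.6) describes the same pair. The change item reads "Participants will record whether there is a perceived change in overall liking of meals due to the tables (yes/no"), and for a perceived change "its magnitude will be quantified using Labeled Affective Magnitude Scale (LAMS"). The instruction that follows, however, is that "they will rate their liking of that specific meal", on a scale where "0 represents the greatest imaginable dislike, and + 100 represents the greatest imaginable like".

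The appetite item is answered on the same form at the same meal. There, participants "will specify the direction of change, indicating whether the tablet was perceived to increase or reduce food intake" (section 3.7.5.5.2).

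Table 6 sets the objective of comparing the change in overall meal liking between MB and placebo. It lists two measures: a daily 0–100 rating, which it calls gLMS, and the self-reported yes/no proportion.

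**The concern.** A yes on the liking item covers a meal liked more and a meal liked less. This matters here because the protocol expects both. The Introduction argues that MB may raise preference for sour and bitter foods. It also argues that MB may add sweetness to food that is already sweet, "which may result in a sensation of oversweetness", with preference and intake then falling. Phase 4 meals are chosen by the participants at home, so one person can record both kinds.

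A higher yes proportion on MB would therefore show that the tablet is noticed, not that it helps. Table 3 appears to rely on the LAMS to supply the missing information, but what it has participants rate is a level of liking. A later analysis plan can change how data are summarised, but it cannot supply a response that the form did not request.

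**Working it through.** The plan states no figure for this outcome, so there is none to reproduce. The check is what each item can identify.

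**1. The yes/no proportion.** Let U be the proportion of tablet meals liked more and D the proportion liked less.

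- Proportion answering yes = U + D
- Net benefit = U − D

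The form gives U + D only. The rates below are assumed for illustration; the protocol gives none.

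| Arm (assumed) | U | D | Yes = U + D | Net = U − D |
|---|---|---|---|---|
| MB, mostly favourable | 40% | 20% | 60% | +20 |
| MB, mostly unfavourable | 20% | 40% | 60% | −20 |
| Placebo | 10% | 10% | 20% | 0 |

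Both MB rows give the same between-arm difference in yes, 60 − 20 = 40 points. The differences in net benefit are +20 and −20.

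**2. Bounds when only the yes rates are known.** Assume 40% yes on MB and 10% on placebo.

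- MB net lies between −40 and +40.
- Placebo net lies between −10 and +10.
- The difference lies between −40 − 10 = −50 and 40 + 10 = +50 points.

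The yes proportion alone does not fix the sign.

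**3. Whether the LAMS supplies the sign of an individual yes.** A change needs two ratings: liking with the tablet minus liking of the same meal without it. Ratings are described only as "For each meal consumed with the tablet", so the second term is missing. For example, a rating of 70 accompanied by yes fits a rise from 50 (+20) and a fall from 90 (−20).

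**4. Whether the LAMS supplies a sign at arm level.** Yes. The scale runs from dislike to like, and Table 6 has treatment as the independent variable. Mean liking can be higher or lower on MB than on placebo. This compares levels across whatever meals participants chose to take with the tablet after allocation. A difference in those choices could shift the mean without any change in liking of a given food.

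**5. The two parallel items side by side.** Table 3 gives appetite three outcomes: eat less, no change, eat more. It gives liking two. Table 6 lists a yes/no proportion for both. For appetite the direction is on the form, so the analysis can still use it; for liking, the text shown describes no such response.

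**The case against.** The strongest reply is that the outcome is not left without direction. Every tablet meal also gets a 0–100 rating from dislike to like, and Table 6 lists a daily 0–100 rating before the yes/no proportion. In the two MB scenarios above, all else equal, mean LAMS would move in opposite directions. Participants also record meal type and main constituents, so liking can be examined by kind of food. This stands. A reader might infer that Phase 4 records only whether liking changed, or that the direction of MB's effect on meal liking is wholly lost. The documents do not support either reading.

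A second reply concerns the stakes. Table 1 places overall meal liking under the primary food-preference outcome, but section 3.7.5 presents it as something additionally explored. Table 6 measures food preferences with the Food Liking Questionnaire, a nine-point directional scale given at baseline, week 6 and week 12. This also stands: the main food-preference analysis does not rest on the yes/no item.

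Third, section 3.7.5.5.2 refers to Table S4 for detailed daily procedures, and that table is not shown. A direction option may exist there. The article text describes one for appetite only.

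None of this repairs the yes/no proportion, which Table 6 still lists as a measure of change in liking, or Table 3's statement about what the LAMS quantifies.

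**Conclusion.** The point holds for the yes/no item and its proportion. As described, that measure cannot separate meals liked more from meals liked less. Under the assumed 40% and 10% yes rates, it is compatible with a net difference anywhere from −50 to +50 points. The LAMS gives a signed between-arm comparison of mean liking, but not the direction or size of the change at a given meal.

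The consequence is limited: one listed measure of one outcome is uninterpretable as to benefit, with a partial fallback, in a feasibility trial of up to 30 participants. The trial's other outcomes are unaffected. The conclusion rests on the article text and assumes that Table S4 adds no direction item. The rates used are illustrative. The change is worth making because it costs little and direction that was not asked for cannot be added at analysis.

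**What to change.** - **Table 3, section 3.7.5.5.1, and the Qualtrics and paper forms:** replace yes/no with three options: liked less, no change, liked more because of the tablet. This mirrors the appetite item.
- **Table 3:** describe the LAMS as rating the level of liking of that meal, not the magnitude of the change.
- **Table 6:** replace the yes proportion with an ordinal comparison between arms, or with separate proportions liked more and liked less. Name the between-arm LAMS comparison, not gLMS, as the level measure. In the same row, reconcile the stated period (week 2 to week 12) with section 3.7.5.5.1, which has daily assessment throughout the 12 weeks.
- **Table S4:** if it already contains a direction item for liking, bring Tables 3 and 6 and section 3.7.5.5.1 into line with it.

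The cost is one more response option on an existing form and a few edited lines, with no added visit or measurement. The drawback is that records already collected as yes/no cannot be merged with the new item and must be reported separately. Table 1 gives the Phase 4 period as May to December 2025, so such records may exist. For those, the between-arm LAMS comparison should carry the interpretation, and the yes proportion should be reported only as the frequency of any perceived change.

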###### Appetite

3.7.5.5.2

Perceived changes in appetite associated with tablet intake will be assessed concurrently with overall liking for the same meals consumed with the MB or placebo tablet throughout the 12‐week intervention period. For each recorded meal, participants will indicate whether they experienced a perceived change in appetite (yes/no) and will specify the direction of change, indicating whether the tablet was perceived to increase or reduce food intake. Appetite responses will be collected using the same Qualtrics link (or hard copy form) and at the same meal occasion as the overall liking assessment. Detailed daily data collection procedures for the follow‐up period (Phase 4) are presented in Table S4.

##### Feasibility Indicators and Reminders

3.7.5.6

As the main outcome of interest, the feasibility indicators, such as recruitment, blinding, allocation, retention, compliance, and adverse effects associated with the intake of the tablets, will be explored and reported (Aschbrenner et al. 2022; Donald 2018; Teresi et al. 2022). Starting from the second visit (after allocating participants to the MB and placebo groups), specific reminders will be sent through each participant's preferred contact method. Table S5 provides details on when and how these feasibility variables will be measured, as well as the types of reminders to be delivered. At the start of treatment (second visit), participants will be provided with an adverse effect recording sheet and instructed to document any adverse effects experienced during the follow‐up period (Supporting Information: Adverse Effect Recording Sheet).

### Data Management and Analysis Plan

3.8

Data completeness, cleaning, and editing will begin with data collection and continue through data entry. Data will be entered into Epi Data Version 4.6 and analyzed using STATA Version 8 software. The data will be checked for missing values and outliers. Descriptive quantitative analysis will be used for reporting results. Categorical variables will be presented using frequencies and percentages. Based on normality assumptions, continuous variables will be reported in mean (±SD) or median (±IQR). Normality will be assessed using both graphical methods (histogram, Q–Q plot, P–P plot) and statistical testing (Shapiro–Wilk test). Homogeneity of variances will be tested using Levene's test. Treatment effects will be determined using mixed models, which account for repeated measures within individuals as well as between‐participant differences in taste perception. A detailed analysis plan for each project phase is provided in Table 6.

**TABLE 6 fsn371640-tbl-0006:** Analysis plan for each analytical objective of the project.

Phases	Analytical objectives	IV	DV	Measurement scale of the dependent variable	Analysis technique

2	To compare the effect of different doses of MB on sourness, and bitterness taste perceptions and overall liking of a hypo‐palatable mixed salad among healthy‐weight Australian adults	Different MB doses ○ Dose 1: ½ tablet (≈170 mg) ○ Dose 2: 1 tablet (≈350) ○ Dose 3: 2 tablets (≈700 mg) Placebo	Ratings for sourness and bitterness taste perception	gLMS (0–100)	As proposed in Phase 1 Additionally, as the sample size was determined using the empirical guideline of at least 10 subjects per predictor variable (Green 1991), and given the complexity in power estimation for mixed models, post hoc sensitivity power analysis will be conducted for planned comparisons. This will determine the minimum detectable effect size based on the achieved sample size and desired statistical power. Recent literature also recommends strengthening sample size justification for such approaches through sensitivity power analyses (Lakens 2022)
			Rating for overall liking	LAMS (0–100)	
			Intake	Served amount of salad minus left over	
	To compare the effect of different doses of MB on sweetness taste perceptions and overall liking of hyper‐palatable SSBs among healthy‐weight Australian adults	Different MB doses ○ Dose 1: ½ tablet (≈170 mg) ○ Dose 2: 1 tablet (≈350) ○ Dose 3: 2 tablets (≈700 mg) Placebo	Sweetness taste perception ratings	gLMS (0–100)	
			Ratings for overall Liking	LAMS (0–100)	
3	To compare the effect of different doses of MB on sourness and bitterness taste perceptions and overall liking of hypo‐palatable mixed salad among overweight or Obese Adults residing in Australia	Different MB doses ○ Dose 1: ½ tablet (≈170 mg) ○ Dose 2: 1 tablet (≈350) ○ Dose 3: 2 tablets (≈700 mg) Placebo	Ratings for sourness and bitterness taste perceptions	gLMS (0–100)	As proposed in Phase 2
			Ratings for overall liking	LAMS (0–100)	
	To compare the effect of different doses of MB on sweetness taste perceptions and overall liking of hyperpalatable SSBs among overweight/obese adults residing in Australia	Different MB doses ○ Dose 1: ½ tablet (≈170 mg) ○ Dose 2: 1 tablet (≈350) ○ Dose 3: 2 tablets (≈700 mg) Placebo	Ratings for sweetness taste perceptions	gLMS (0–100)	
			Ratings for overall Liking	LAMS (0–100)	
4	To measure the feasibility of the treatment protocol, study procedures and outcome	Treatment ○ MB ○ Placebo Follow‐up duration	Retention rate, Compliance rate, adverse effects, recruitment and allocation success rate	Frequency and descriptive explanations	Descriptive statistics ○ Mean (±SD) for normally distributed data, otherwise Median (±IQR) ○ Counts and frequencies
	To measure the effect of MB consumption on food preferences in overweight or obese adults living in their natural environment (i.e., at home).	Treatment ○ MB ○ Placebo Measurement time (baseline, mid‐protocol, completion)	Changes in food preferences	FLQ as a continuous scale (Food liking score) on three occasions (at baseline, week 6, week 12, and at the end line)	Descriptive statistics ○ Mean (+SD) for normally distributed data, otherwise Median (+IQR) ○ Counts and frequencies The treatment effect will be assessed using LMM or GLMM, as proposed in Phase 1. Given that this is a feasibility trial, a sensitivity power analysis will be conducted to determine the minimum detectable effect size based on the available sample size and the desired statistical power. The analysis will be conducted on an intention‐to‐treat basis
	To investigate the effect of MB consumption on the energy intake of overweight or obese adults living in their natural environment (i.e., at home)	Treatment ○ MB or ○ Placebo Measurement time (baseline, mid‐protocol, completion)	Changes in energy intake	Diet intake converted to kilo calories (at baseline, week 6, week 12)	
	To determine the effect of MB consumption on the diet quality of overweight or obese adults living in their natural environment (i.e., at home)	Treatment ○ MB or ○ Placebo Measurement time (baseline, mid‐protocol, completion)	Changes in diet quality score	Total ARFS score and each food group ARFS score (at baseline, week six, week 12)	
	To determine the effect of MB consumption on overall liking of mixed meals served as breakfast, lunch, dinner, and snacks in overweight or obese adults living in their natural environment (i.e., at home)	Treatment ○ MB or ○ Placebo Measurement time (daily throughout the follow‐up period)	Comparing the change in overall liking of the meal (served as breakfast, lunch, dinner, snack)	gLMS measured daily from week 2 to week 12 (0–100) Proportion (self‐reported yes/no)	

	To determine the effect of MB consumption on the appetite for different foods in overweight or obese adults living in their natural environment (i.e., at home)	Treatment ○ MB or ○ Placebo Measurement time (daily throughout the follow‐up period)	Comparing the change in appetite	Proportion (self‐reported yes/no)	
To measure the effect of MB consumption on anthropometric and body composition measurements of overweight or obese adults living in their natural environment (i.e., at home)	Treatment ○ MB or ○ Placebo Measurement time (baseline, mid‐protocol, completion)	Changes in anthropometric and body composition measures	Weight, BMI, WC, WHtR, FFM, Body Fat Percentage, Body water (at baseline, week 6, week 12)		

Abbreviations: FFM, fat‐free mass; FM, fat mass; WC, waist circumference; WHtR, Waist‐to‐height ratio.

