### Data Collection Tools

3.6

Table 3 describes measurement tools for each key outcome variable and covariates in each project phase.

**TABLE 3 fsn371640-tbl-0003:** Measurement tools and their description for key variables in each phase of the project.

Phases	Variable to be measured		Tool	Description	References
Phase 1	Sour, bitter, tart and sweet taste perceptions of individual food‐based solutions and food items		Generalized Labeled Magnitude Scale (gLMS)	Ranges from 0 (barely detectable) to 100 (the strongest sensation of any kind). Participants will establish these boundaries (no sensation to strongest imaginable) before rating items	Green et al. (1996)
Phases 2 and 3	Overall liking of hypo‐palatable mixed vegetarian salad and hyper‐palatable SSB		Labeled Affective Magnitude Scale (LAMS)	Ranges from 0 (greatest imaginable dislike) to +100 (greatest imaginable like). Study participants will be asked, “How much do you like/dislike this food item? (please put a slash (/) mark somewhere on the line).”	Schutz and Cardello (2001)
	Sourness and bitterness taste perceptions of hypo‐palatable mixed vegetarian salad and sweetness taste perceptions of hyper‐palatable SSBs		Generalized Labeled Magnitude Scale (gLMS)	Ranges from 0 (barely detectable) to 100 (the strongest sensation of any kind). Before rating items, participants will establish these boundaries (no sensation to the strongest imaginable)	Green et al. (1996)
	Intake of the hypo‐palatable mixed vegetarian salad		The difference between the amount served and the amount left over	At both the pre‐test and post‐test sessions, participants will be provided with a fixed portion of mixed salad weighing 117 g, which corresponded approximately to half a serve of vegetables and half a serve of fruit according to the Australian Dietary Guidelines. Participants will be instructed to consume as much of the provided salad as they desired. Each portion will be weighed prior to serving, and any leftovers will be weighed immediately after consumption. Actual intake will be calculated as the difference between the amount served and the amount remaining	National Health and Medical Research Council (2013)

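### Table 6 lists Phase 4 meal liking on a scale and over weeks that differ from its collection, and reduces appetite change to a yes/no proportion without its direction

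*Protocol article*

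**What the plan says.** **Meal liking, as collected.** Table 3 (section 3.6) has participants say whether the tablet changed their liking of a meal and then rate that meal: "Then using LAMS, in which 0 represents the greatest imaginable dislike". Section 3.7.5.5.1 repeats this and ties it to treated meals: "For each meal consumed with the tablet, participants will indicate whether they experienced a perceived change in overall liking", and they "will rate their liking using the LAMS". That section has the ratings made daily over the 12 intervention weeks, and footnote b of Table 5 has them recorded throughout the 12-week follow-up.

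**Meal liking, as analysed.** The Phase 4 row of Table 6 names the dependent variable as a change in overall liking. Its measurement-scale column reads "gLMS measured daily from week 2 to week 12" and then adds a self-reported yes/no proportion. Another column of the same row gives the measurement time as daily over the whole follow-up.

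**Appetite, as collected.** Under section 3.7.5.5.2, participants give a yes/no answer for each recorded meal and "will specify the direction of change, indicating whether the tablet was perceived to increase or reduce food intake". Table 3 describes the same item with three answers: eating less, no change, eating more.

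**Appetite, as analysed.** Table 6 gives the dependent variable as "Comparing the change in appetite" and the scale as a self-reported yes/no proportion, with no mention of direction.

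**The concern.** An analyst who follows Table 6 literally would look for a taste-intensity rating that Phase 4 does not collect, would start a week after treatment begins, and would try to form a change score with nothing to subtract. For appetite, the analyst would count a meal at which the tablet led to eating more and one at which it led to eating less as the same event.

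This matters because Table 1 places overall meal liking under the Phase 4 primary outcomes, and section 3.4.3 rests the sample size on a previous crossover trial's effects on overall meal liking. If scale, window and outcome definition are not settled in advance, they will be chosen once the data are visible. A directionless appetite proportion also cannot show whether the tablet was perceived to raise or lower intake, which is what the direction item was added to capture.

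**Working it through.** **1. The stated sample size.** Section 3.4.3 starts from 20 participants and 32% attrition: 20 / (1 − 0.32) = 29.4, rounded up to 30, or 10 / 0.68 = 14.7, rounded up to 15 per arm. The figure reproduces, and nothing below depends on it.

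**2. Scale.**
- Table 3 (Phase 4) and section 3.7.5.5.1: LAMS.
- Table 6, Phases 2 and 3: LAMS for liking, gLMS for taste.
- Table 6, Phase 4 liking row: gLMS.
- Definitions in Table 3: the gLMS runs from barely detectable to the strongest sensation; the LAMS runs from dislike to like.

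The Phase 4 row is out of line with the collection sections and with the rest of its own table. No Phase 4 gLMS collection is described in the article.

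**3. Window.** Tablets are handed out at the second visit, at the end of the baseline week (section 3.7.5.2), which Table 5 labels week 0. Week 1 is therefore a treated week.
- Weeks 1 to 12: 12 × 7 = 84 days.
- Weeks 2 to 12: 11 × 7 = 77 days.
- Difference: 84 − 77 = 7 days; 7 / 84 = 8.3%.

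Counting the baseline week as week 1 does not reconcile the two, because 12 tablet weeks would then run from week 2 to week 13.

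**4. Change in liking.** Ratings are attached to meals taken with a tablet, so no earlier LAMS value is described from which to compute a within-person difference. A between-arm comparison of on-treatment level does not need one. With one baseline and one follow-up value of equal variance and correlation r, the variance of the arm contrast relative to follow-up only (set at 1) is 2(1 − r) for a change score and 1 − r² for baseline adjustment:

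| r (assumed) | Follow-up only | Change score | Baseline-adjusted |
|---|---|---|---|
| 0.2 | 1 | 1.60 | 0.96 |
| 0.5 | 1 | 1.00 | 0.75 |
| 0.8 | 1 | 0.40 | 0.36 |

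The missing baseline costs the within-person change and some precision. It does not remove every treatment-effect estimate. The documents give no value for r.

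**5. Appetite direction.** With assumed rates, P(yes) = P(less) + P(more) and net = P(more) − P(less):

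| Less | More | P(yes) | Net |
|---|---|---|---|
| 30% | 10% | 40% | −20 points |
| 20% | 20% | 40% | 0 |
| 10% | 30% | 40% | +20 points |

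Arms in the first and third rows differ by 40 points in net direction, yet the difference in the yes proportion is zero.

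**The case against.** A reader might infer that neither the change in liking nor the change in appetite can be estimated. The documents do not support that. The same Table 6 cell lists the yes/no proportion for liking. A perceived change is self-anchored for each meal, so it needs no earlier rating and can be compared between arms. LAMS levels on treatment can also be compared in the mixed model. Appetite direction is in the data, so the fault lies in the specification. One limit remains: the liking yes/no item is itself unsigned, so its proportion should be read beside the LAMS level.

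A reader might also infer that the first treated week is lost. It is collected either way, and the Table 6 row contradicts itself on the window, so it does not fix an exclusion.

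It is fair to say that the gLMS entry looks like a slip. Both scales run from 0 to 100, and correcting one word settles it. The outcome's status is also mixed: Table 1 puts meal liking under primary outcomes, while section 3.7.5 describes liking of mixed meals and appetite as additional explorations, and the abstract measures food preferences with the FLQ. Table 1 lists appetite among other outcomes, and energy intake is measured separately by food records and recalls. The appetite rates above were chosen to cancel exactly; they show a possibility, not an expected size.

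Finally, Table S4, which details the daily procedures, is not in the text at hand, so a pre-tablet rating cannot be wholly excluded. Section 3.7.5.5.1 and footnote b of Table 5 nevertheless tie the ratings to meals taken with MB or placebo.

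These points narrow the finding. They do not remove the conflicts over scale, window and appetite direction.

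**Conclusion.** The concern holds as a set of specification conflicts in Table 6. For meal liking, the scale is wrong against two other places in the article, and the window is short by one treated week (8.3% of 84 days) against section 3.7.5.5.1 and against its own row. The named change has no described pre-tablet value behind it. The on-treatment LAMS level and the proportion reporting change remain estimable between arms. The missing baseline weighs somewhat more here than in a clearly randomised trial, because section 3.1 calls the designs quasi-experimental and section 3.7.5.2 says only that participants are allocated.

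For appetite, the analysis as written can hide opposite effects entirely. How far it would do so depends on response rates that the documents do not give.

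The text conflicts rest on no assumption. The precision and masking figures are illustrations under stated assumptions. The consequence is moderate: this is a feasibility phase and the data are collected, but one affected outcome is listed as primary in Table 1.

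**What to change.** In the Phase 4 rows of Table 6:

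- **Scale and window:** replace the gLMS entry with LAMS, week 1 to week 12, to agree with Table 3 and section 3.7.5.5.1.
- **Liking outcome:** define it as the between-arm difference in on-treatment LAMS level, together with the proportion of meals with a perceived change, and stop calling the LAMS part a change.
- **Appetite:** analyse it as a three-level ordered outcome (less, no change, more) with an ordinal mixed model, or report the less and more proportions separately. The second is simpler if the ordinal model is unstable with up to 30 participants.

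These are wording changes and need no new data.

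**Optional:** collect LAMS meal ratings in the untreated baseline week and adjust for their mean. That would supply a reference level and probably some precision. It also adds burden: that week already carries a 3-day food record (section 3.7.5.1), and the daily questionnaire is first given at the second visit (section 3.7.5.3). Untreated meals may also differ from treated ones, since lime is encouraged with the tablets (section 3.7.5.2). It is a reasonable choice either way.
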